### Data collection and management

The outcomes will be measured during the intervention and 28 days after the patients are enrolled in the group. The data on the duration of different respiratory support, hospital and ICU lengths of stay, and hospitalisation cost will be collected at discharge or the 28th day after enrolment, whichever occurs first. (The data collection schedule is shown in Table 1). Trained nurses will assess the Borg scale score and fill in the bedside inspection forms (Additional file 6) with average vital signs within 3 min at each allotted timepoint and position change time of each round. Supervisors will examine and transcribe inspection forms every day. Two trained researchers who do not know patients’ allocations will check and collect all other data extracted from the electronic medical record system, including data on withdrawn patients. The main researchers will explain every detail of the parts each researcher is responsible for through online or physical training with a set of standard teaching materials, check the training effect through a test, and give one-to-one guidance to every researcher according to their results.

**Table 1 Tab1:** Data collection schedule

Study Period	Timepoint	Assessments
Enrolment	Day 0–1	Eligibility
		Informed consent
Allocation		Baseline information
		PaO_2_/FiO_2_ ratio after receiving HFNO therapy for 2 h
Post-allocation	During interventions (Day 1–termination)	Vital signs
		PaO_2_/FiO_2_ ratio
		Borg scale
		Position changing time (experimental groups only)
		ROX index
		Special treatments
		Respiratory support
		Adverse events
	At discharge/Day 28	Hospitalisation cost
		Number of hours using HFNO
		Number of hours using advanced respiratory support mode
		Number of hours using conventional oxygen therapy
		Length of hospital and ICU stay
Close-out	At Day 28	Death
		Endotracheal intubation

The confidentiality of the data will be preserved when the coded, anonymised data are transmitted and stored at the location of the statistician in charge of the final analysis.

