## Methods

### Trial design

This is a three-arm, parallel-group, multicentre, randomised controlled, open-label exploratory trial. A total of 583 will be randomly assigned to be placed in the semi-recumbent position (control group), the prone position (experimental Group A), and the lateral position (experimental Group B) at a ratio of 1:1:1. The follow-up period was 28 days. We will conduct and report this trial according to Standard Protocol Items: Recommendation for Interventional Trials. The trial design flowchart is detailed in Fig. 1.

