### Indications for terminating the intervention

When the patient’s flow velocity is < 30 L/min and the PaO_2_/FiO_2_ ratio is > 300 mmHg for 6 h [38];The patient can maintain SpO_2_ at 92%–96% [39] with a respiratory rate no more than 25–30 times per minute while using conventional oxygen therapy (nasal prongs, facemask with or without reservoir or Venturi mask with less than 8 litres per minute and the fraction of inspired oxygen less than 35%).The patient’s condition worsens, noninvasive ventilation or endotracheal intubation is needed (see more in “Indications for noninvasive ventilation” and “Indications for endotracheal intubation” section) or death occurs.

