#### Secondary outcomes

28-day intubation rate (intubation is defined as endotracheal intubation and receiving invasive mechanical ventilation);28-day all-cause mortality(defined as death caused by all kinds of diseases within 28 days after randomisation);Change in the daily PaO_2_/FiO_2_ ratio (measured every morning around the same time) during intervention;Change in daily Borg scale score;Daily and total position changing time;Change in daily ROX index: SpO_2_/FiO_2_ to respiratory rate;Number of hours receiving HFNO therapy;Number of hours receiving noninvasive mechanical ventilation and invasive mechanical ventilation;Treatment failure rate (defined as patients who receive noninvasive, invasive ventilation or die after taking assigned positions);The incidence of adverse events;Length of hospital stay and ICU stay.Hospitalisation cost.

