### Adverse outcomes and precautions

The probabilities of adverse events, including pressure injury, arrhythmia, asphyxia, and unplanned extubation (the definitions are seen in Additional file 7), have been reported to be small [16].

By fully educating patients with a teaching video before the start of the trial, we will instruct them to take a standard lying position and teach them how to adjust their positions and decompress pillows to make them feel comfortable and avoid pressure injuries. All kinds of tubes will be properly fixed and secured with the investigators’ help. Patients will be told to sit up or take the supine position and ring the bell to call the nurse immediately in case of palpitation, chest tightness, or dyspnea to stop the development of threats.

Although the probability of fatal adverse events occurring is low, there is still a risk of cardiac arrest [3]. Observations by clinicians indicate that patients’ intolerance and cardiac discomfort generally occur within the first hour of treatment. To ensure patients’ safety, for the participants in the experimental groups (Group A and Group B), the patients’ vital signs will be consistently monitored; the investigators will check each patient at the 15-min, 30-min, and 1-h time points, and then every 1 h using a standardised inspection checklist (Additional file 5). The participants’ vital signs in the control group will be checked every 2 h. We encourage nurses to use special symbols that their leaders do not know to represent the event when adverse outcomes happen, to increase reporting behaviour.

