### Statistical methods for the primary and secondary outcomes

Analysis of variance will be used for ventilator-free days in 28 days, the number of hours using HFNO, noninvasive ventilation, invasive mechanical ventilation, length of hospitalisation, and hospitalisation cost. When it indicates that at least one group is significant, the Bonferroni correction will be applied.

For the 28-day mortality rate and 28-day intubation rate, we will conduct a survival analysis with the Kaplan-Meier method. We will compare the mortality and intubation rates of the three study groups using a log-rank test. We will use the Cox proportional hazards model to detect the relationship between diagnosis, onset time, PaO_2_/FiO_2_ ratio change, the duration of changing positions, and total position changing time.

Other secondary outcomes, such as the change in the PaO_2_/FiO_2_ ratio, ROX index, Borg scale score within the groups, will be compared with a paired repeated measures analysis of variance or generalised estimating equation based on the integrity of the data. The incidence of adverse events will be analysed using either the chi-square test or Fisher’s exact test. Univariate and multivariate analyses of risk factors for prone position failure will be performed with logistic regression.

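### Adverse events are scheduled only until the intervention ends, so crude incidence is compared over observation times that depend on outcome and may differ by arm

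*Protocol article*

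**What the plan says.** All references are to the protocol article.

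- **Data collection and management, Table 1.** Adverse events sit in the post-allocation block labelled "During interventions (Day 1–termination"). The discharge/Day 28 row holds cost, hours of each type of respiratory support, and length of stay. The Day 28 close-out row holds death and endotracheal intubation. Adverse events appear in neither.
- **Indications for terminating the intervention.** There are two recovery criteria: low flow with a good oxygenation ratio for 6 h, or adequate saturation and respiratory rate "while using conventional oxygen therapy". The third criterion is deterioration, where "noninvasive ventilation or endotracheal intubation is needed", or death.
- **Trial design.** "The follow-up period was 28 days".
- **Secondary outcomes.** The entry is "The incidence of adverse events", with no time window.
- **Statistical methods for the primary and secondary outcomes.** "The incidence of adverse events will be analysed using either the chi-square test" or Fisher's exact test. Time at risk is not mentioned.
- **Adverse outcomes and precautions.** The events named are those "including pressure injury, arrhythmia, asphyxia, and unplanned extubation".
- **Data collection and management, opening sentence.** "The outcomes will be measured during the intervention and 28 days after the patients are enrolled in the group". It does not say which outcomes belong to which period.

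**The concern.** A crude proportion compares arms fairly only if patients in each arm are watched for comparable periods, or for periods unrelated to treatment. Here the watch ends at a post-randomisation event, and the positions are being tested because they may change when that event happens. Two arms with the same underlying risk could record different incidences simply because one was observed for longer.

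Events that surface late are also lost. A pressure injury caused by positioning but noticed after positioning has stopped has no scheduled place in Table 1.

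At stake is the between-arm safety comparison, a secondary outcome. The primary analysis is not affected. The matter is one of a rule the article states, not of detail left to a fuller document: the schedule gives the window an explicit end.

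**Working it through.** The plan states no figure for this point, so there is none to reproduce. The check has three steps.

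**1. The passages side by side.**

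| Item | Observed until |
|---|---|
| Death, endotracheal intubation | Day 28 |
| Hours of respiratory support, length of stay, cost | Discharge or Day 28 |
| Adverse events | Termination of the intervention |
| Termination | Recovery, need for noninvasive ventilation or intubation, or death |

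Only the adverse-event row closes at a point defined by the patient's clinical course. The sample-size section expects that course to differ by arm: 19 ventilator-free days in control, 23 in prone, 22 in lateral. Time to termination may therefore differ too.

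**2. Direction.** Let windows close at daily rate f through failure and r through recovery. Mean window length is then about 1/(f + r). A position that works would lower f, which lengthens the window, and could raise r, which shortens it. The net change has the sign of the larger effect, and the article gives neither rate by arm. The direction is undetermined.

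**3. Size, as an illustration only.** Assume a constant daily event hazard h, equal in both arms, and an exponential time to termination with mean m days, capped at 28. Both h and m are assumptions, because the article gives neither.

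P(event recorded) = h/(h + 1/m) × [1 − exp(−28(h + 1/m))]

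Worked case, h = 0.02:
- m = 4: 0.02/0.27 × [1 − exp(−7.56)] = 0.074
- m = 6: 0.02/0.1867 × [1 − exp(−5.227)] = 0.107
- Ratio: about 0.69

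| h per day | 5 vs 6 days | 4 vs 6 days | 3 vs 7 days | Full 28 days, either arm |
|---|---|---|---|---|
| 0.01 | 4.7% vs 5.6% (0.84) | 3.8% vs 5.6% (0.68) | 2.9% vs 6.5% (0.45) | 24.4% |
| 0.02 | 9.1% vs 10.7% (0.85) | 7.4% vs 10.7% (0.69) | 5.7% vs 12.2% (0.47) | 42.9% |
| 0.03 | 13.0% vs 15.2% (0.86) | 10.7% vs 15.2% (0.70) | 8.3% vs 17.2% (0.48) | 56.8% |

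The last column is 1 − exp(−28h), the same in both arms, so the ratio is 1.0. It is an upper bound, since it assumes the hazard persists unchanged after positioning stops. The ratios hardly depend on h. They depend on how far mean window length differs between arms, which is unknown.

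**The case against.** **The opening sentence of the data collection section mentions 28 days.** Adverse events are a listed outcome, so one could read them as followed that long. The sentence does not allocate outcomes to periods, however, while Table 1 does and puts adverse events in the first. What stands is that the two passages need reconciling.

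**The gravest consequences are captured elsewhere.** This is correct. Death, intubation, ventilation hours and length of stay run to discharge or Day 28, and treatment failure is a secondary outcome. The gap is limited to other, non-fatal events after termination.

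**An on-intervention window suits harms of positioning.** This is partly right. The section on adverse outcomes says that intolerance and cardiac discomfort generally arise within the first hour of treatment. For such events the later length of the window matters little, and the constant-hazard illustration overstates the effect. The argument is weaker for pressure injury, which may be noticed later. The on-intervention view is worth keeping, but it should not be the only view when it is analysed as a crude proportion.

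**Stronger readings the article does not support.** A reader might infer that the arm failing sooner will look safer. That ignores closure of the window by recovery. A reader might also infer that unplanned extubation can never be recorded, because intubation ends the window. That presumes the term means the endotracheal tube. The definition is in Additional file 7, which is not shown, and the same section speaks of securing tubes of all kinds, so other tubes may be meant.

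**Conclusion.** The point holds in a limited form. As scheduled, adverse events are observed up to an outcome-dependent endpoint and compared as crude incidence, so unequal observation time can create or hide a difference between arms. Non-fatal events noticed after termination can be missed.

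The size cannot be stated from the article. Under equal constant hazards, the recorded ratio would be about 0.85 for mean windows of 5 versus 6 days, about 0.7 for 4 versus 6, and 0.45 to 0.48 for 3 versus 7, where 1.0 is the truth. If mean windows are equal across arms, or events cluster in the first hour, the distortion is small or absent. Which arm would be favoured is unknown.

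The conclusion rests on reading Table 1 as the operative schedule. If the full protocol follows adverse events to Day 28, only the table and the outcome definition need correcting.

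**What to change.** 1. In Table 1, add adverse events to the discharge/Day 28 row for every randomised patient in all three arms, withdrawn patients included. The record extraction already planned there can supply them.
2. In Secondary outcomes, define the window as randomisation to Day 28, with in-hospital events captured to discharge if that is earlier. Report time at risk by arm. This is needed because length of stay is itself an outcome, so a window ending at discharge is not fully common to the arms.
3. Keep events during the intervention as a second table, expressed per time at risk.
4. Reconcile the opening sentence of Data collection and management with Table 1, so that each outcome has one stated period.

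The cost is one table entry, one field at an existing extraction, one sentence in the outcome definition, and some extra record review. The wider window will also admit more background events from the ventilated phase, which may dilute a signal due to positioning. The second table guards against that.

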### Data monitoring

The data monitoring committee will be composed of a nurse, a doctor, and a statistician independent of the investigators and without competing interests. They will check data integrity, accuracy, authenticity, and timeliness daily. They will make suggestions to ensure data quality and suggest stopping the trial if safety issues arise.

### Adverse outcomes and precautions

The probabilities of adverse events, including pressure injury, arrhythmia, asphyxia, and unplanned extubation (the definitions are seen in Additional file 7), have been reported to be small [16].

By fully educating patients with a teaching video before the start of the trial, we will instruct them to take a standard lying position and teach them how to adjust their positions and decompress pillows to make them feel comfortable and avoid pressure injuries. All kinds of tubes will be properly fixed and secured with the investigators’ help. Patients will be told to sit up or take the supine position and ring the bell to call the nurse immediately in case of palpitation, chest tightness, or dyspnea to stop the development of threats.

Although the probability of fatal adverse events occurring is low, there is still a risk of cardiac arrest [3]. Observations by clinicians indicate that patients’ intolerance and cardiac discomfort generally occur within the first hour of treatment. To ensure patients’ safety, for the participants in the experimental groups (Group A and Group B), the patients’ vital signs will be consistently monitored; the investigators will check each patient at the 15-min, 30-min, and 1-h time points, and then every 1 h using a standardised inspection checklist (Additional file 5). The participants’ vital signs in the control group will be checked every 2 h. We encourage nurses to use special symbols that their leaders do not know to represent the event when adverse outcomes happen, to increase reporting behaviour.

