### Control group

Patients in the control group will take the semi-recumbent position (with the bed head elevated 30°–40°) which is the regular position taken by patients. Nurses will routinely instruct the patients to roll over and check vital signs every 2 h. Arterial blood gas will be measured daily. Patients in this group will not take the prone or lateral position unless their doctors think it is necessary.

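### Adverse events are looked for more often in the two position arms than in control, so adverse-event incidence against control is confounded with detection, chiefly for transient events

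*Protocol article*

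**What the plan says.** All references are to the protocol article.

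- **Position arms (Adverse outcomes and precautions).** For Groups A and B, "vital signs will be consistently monitored", and in addition "the investigators will check each patient at the 15-min, 30-min, and 1-h time points, and then every 1 h using a standardised inspection checklist". The stated reason is patient safety.
- **Control arm.** The same section says that "vital signs in the control group will be checked every 2 h". The Control group section gives the same interval as routine nursing: "Nurses will routinely instruct the patients to roll over and check vital signs every 2 h".
- **Outcome and test.** "The incidence of adverse events" is listed under Secondary outcomes. Under Statistical methods for the primary and secondary outcomes, "The incidence of adverse events will be analysed using either the chi-square test or Fisher’s exact test". That sentence does not name the groups; a comparison across the three arms is the natural reading.
- **Events.** The adverse events are described as "including pressure injury, arrhythmia, asphyxia, and unplanned extubation", with definitions in an additional file that is not shown. Their probability is called small and no rate is given.

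**The concern.** How often a patient is observed depends on the allocated arm. An event that comes and goes can be recorded only if somebody is looking or the patient calls, so the same true risk can give more recorded events in Groups A and B than in control. The extra checks are densest in the first hour, which is also when the protocol expects most intolerance and cardiac discomfort.

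The direction of the bias is known. It could produce apparent harm from prone or lateral positioning where there is none, or mask a true reduction. The analysis cannot repair this afterwards, because events never observed in control are not in the data. The trial's first objective concerns the effects of the two positions, so their safety against control will be read.

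**Working it through.** **The plan's own figures.** There is none for adverse events. The only design figure used here is the number per arm. The protocol's 486 is reproduced by a one-way analysis of variance with means 19, 23 and 22 and a common SD of √((13² + 12² + 11²)/3) = 12.03: 162 per arm, power 0.80. Enrolment of 583 gives 583/3 ≈ 194 per arm, used below.

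**Step 1: scheduled checks.** Over L hours in position, Groups A and B have 2 checks (15 and 30 min) plus one at each full hour; control has L/2 on average. The 3.5 h and 8 h lengths are durations discussed in the Background and Discussion.

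| Time | Position arm | Control | Ratio |
|---|---|---|---|
| 1 h | 3 | 0.5 | 6.0 |
| 3.5 h | 5 | 1.75 | 2.9 |
| 8 h | 10 | 4 | 2.5 |

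Monitoring of vital signs in Groups A and B comes on top of this.

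**Step 2: capture of a transient event.** Suppose an event of d minutes, with uniform onset, is seen only if in progress at a check. Capture is min(1, d/interval). In the first hour of a session it is [min(d,15) + min(d,15) + min(d,30)]/60.

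| Duration | First hour in position | Hourly checks | Control, 2-hourly |
|---|---|---|---|
| 15 min | 45/60 = 75% | 15/60 = 25% | 15/120 = 12.5% |
| 30 min | 60/60 = 100% | 30/60 = 50% | 30/120 = 25% |
| 120 min or more | 100% | 100% | 100% |

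An event that persists is therefore found under either schedule.

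**Step 3: effect on one position-versus-control test.** Assumptions, none of them given by the document: equal true risk p; a share s of events is transient; the position arm records every event; control records all other events but only a fraction c of the transient ones (c = 0.25 for 30 min, 0.125 for 15 min). The recorded risk in control is p × [1 − s(1 − c)]. For example, with p = 10%, s = 0.5 and c = 0.25, it is 10% × (1 − 0.5 × 0.75) = 6.25%. The chance of a false p<0.05 is the exact sum of binomial probabilities over all pairs of counts, with 194 per arm, for which the two-sided Fisher p-value is below 0.05.

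| Transient share s | Recorded in control, p = 10% (30 / 15 min) | False p<0.05, p = 10% | False p<0.05, p = 5% |
|---|---|---|---|
| 0 | 10% | 3.3% | 2.8% |
| 0.25 | 8.1% / 7.8% | 7.0% / 8.5% | 4.2% / 4.8% |
| 0.5 | 6.3% / 5.6% | 21% / 29% | 10% / 13% |
| 1 | 2.5% / 1.25% | 85% / 97% | 46% / 69% |

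With all events transient, the chance is 9% to 13% at p = 2% and about 1% at p = 1%.

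**Step 4: weaker monitoring in the position arms.** If Groups A and B had only hourly checks and all events were transient, capture would be 25% v 12.5% (15 min) or 50% v 25% (30 min). The false-positive chance is then about 6% to 17% at p = 10% and 1% to 6% at p = 5%.

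**Step 5: three-arm chi-square test.** A simulation with 194 per arm, p = 10%, full capture in both position arms and control missing half of the check-dependent events gives a false-positive rate of 6.6%, 12.6% and 45.1% when 25%, 50% and 100% of events depend on checks. With equal capture it is about 5%.

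**The case against.** The strongest reply is that this is a safety measure in an exploratory trial and that most of the named events do not depend on check frequency. Pressure injury persists; asphyxia and unplanned extubation are overt. The checks start at 15 minutes, so they appear tied to time in position and the gap need not last all day. The wording on monitoring does not say that it is continuous. Patients are told to ring the bell, nurses are encouraged to report, and Table 1 lists adverse events without limiting them to an arm. Much of this stands, and it narrows the point to transient events. It does not remove the point: bell calls need symptoms and are described within the positioning instructions, and neither nurse reporting nor blinded extraction from records can recover an event that nobody saw.

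Three stronger readings are tempting but not supported:

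- **That the adverse-event comparison mainly measures how often each arm is observed.** That needs nearly all events to be transient. The document gives no event mix, and prone and lateral share one schedule.
- **That control has no checklist.** This is inferred from silence. Data collection and management has nurses complete bedside forms at allotted times without limiting this to an arm, and the forms are not shown.
- **That the primary outcome is biased too, because respiratory rate and SpO2 appear among the indications for noninvasive ventilation.** Those indications also use blood gases and the ROX index, and doctors make the evaluation. Finding a sustained deterioration up to 2 h later is 2/24 ≈ 0.08 day on an outcome counted in days. No calculation supports a material effect.

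A last objection concerns the remedy: removing events found at extra checks from every comparison could hide real positional harm. That is right, and the all-events comparison should stay.

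**Conclusion.** The point holds in limited form. Ascertainment is more intensive by design in both position arms, adverse-event incidence is tested, and nothing in the document equalises detection. Each position-versus-control comparison is biased towards more recorded events in the position arm, chiefly for transient events such as arrhythmia. Prone versus lateral is unaffected.

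The bias can be slight or dominant. The calculated range runs from little above the test's own error rate, when few events are transient or events are rare, to near-certain false significance in the extreme case where every event is brief and the position arms miss none. Event risk, duration, transient share and capture are all assumptions, so no single figure should be quoted as the expected effect. The plan should be amended on this point; its efficacy analyses are not called into question by it.

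**What to change.** Keep all additional checks in Groups A and B. Then state in the protocol and on the case forms that:

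1. The same inspection checklist is completed at control's existing 2-hourly check and at matching 2-hourly times in both position arms.
2. The formal position-versus-control comparison uses events found at those common times, plus persistent or overt events documented in the record in any arm.
3. Events found only at the additional position-arm checks are flagged and reported separately by arm.
4. The comparison of all recorded events is shown beside the formal one, with a statement that it is subject to detection bias.

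The cost is wording, a flag on the form, one checklist at a control round that already takes place, and matching 2-hourly times in the position arms, which the document does not now state. Fewer events enter the formal comparison, and brief position-related events found only at the extra checks appear only in the separate report and the caveated all-events table. None is lost from reporting.
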